### Procedure

2.4

This study is approved and overseen by an Institutional Review Board (iRISID-2023-1533) and complies in full with the Helsinki Declaration for the protection of human subjects.

Participants are recruited from a variety of sources including two research registries at the study site, as well as clinical programs at the site and others in the geographical vicinity. Recruitment began in December, 2023 and is expected to continue until December, 2026. Prospective participants are screened for eligibility over the phone after expressing interest in the study and assenting to screening. Eligible participants are invited to an in-person session that includes written consent, administration of T1 measures listed in Table 1, and screening by both the study physician and the study Physical Therapist. These screenings include a review of systems and assessment of vital signs, lower extremity range of motion, and mobility. Exercise tolerance is evaluated using the modified Bruce protocol (74). Following the physical/ medical screening and the T1 evaluation, participants are given the Actigraph and instructed to wear it continuously for 7 days as they go about their normal routines in the home and community. Participants are given postage-paid padded envelopes for returning the devices.

After all baseline data including the Actigraph data are collected, participants are randomized 1:1 to IT or WL. Randomization uses a sequence of permuted blocks randomly selected from sizes 6, 9, and 12. The randomization sequence was created by the study statistician and is kept in a securely housed spreadsheet which kept all but the current treatment assignment obscured from view. To maximize equipoise and minimize attrition, participants are informed that the randomization is to “one baseline evaluation” or “two baseline evaluations 10 weeks apart.” WL participants receive periodic contacts from research staff reminding them of their upcoming activities in the program. After this initial 10-week period, the primary outcome is measured with another 7-day Actigraph wear period, followed by telephone administration of the outcome measures listed in Table 1.

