### Data analysis

2.6

For the primary endpoint (*Hypothesis 1a*: **primary hypothesis**) and each of the secondary endpoints (*Hypothesis 1b*), the mean change from T1 to T2 in the IT group will be compared to the mean change from T1 to T2 in the WL group using the two-sided two-sample t-test with alpha = 0.05. The mean change in each group and the mean difference between changes in IT vs. WL group will be estimated with the corresponding 95% confidence interval. If the normal distribution assumption is not appropriate for patient-specific changes in one or both groups, then the two-sided two-sample Wilcoxon test will be used instead of the t-test. We will employ intent-to-treat for the *primary analysis*, and as such, we will make every attempt to collect T2 outcome data on all randomized participants regardless of treatment received. Per current recommendations (82–84), we will use multiple imputation to account for missing T2 data, and evaluate missingness assumptions (by comparing available data for participants with complete vs. missing T2). If the assumption of the data being *missing at random* is not appropriate, the imputations will be performed using the methods specifically developed for data *missing not at random* (85). As a *secondary analysis* we will perform a complete-case analysis with dropouts excluded. With the proposed sample size of 35 subjects per arm and assuming up to 15% loss to follow-up, we expect to have at least 30 subjects per arm available for analysis. The sample size of 30 subjects per arm provides 81% power to detect the mean difference between changes in IT vs. WL arms corresponding to the effect size of 0.75 (effect size for the primary endpoint as reported in Clanchy et al. (24) using the two-sided two-sample t-test with alpha 0.05.

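### A comparison of participants with and without T2 data decides whether the primary imputation assumes MAR or MNAR, but it cannot tell the two apart

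*Protocol article*

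**What the plan says.** All the relevant text is in the Data analysis section (2.6) of the protocol article. The T1 to T2 change is compared between immediate treatment (IT) and waitlist (WL) "using the two-sided two-sample t-test with alpha = 0.05". The primary analysis is by intention to treat, T2 data are to be sought from everyone randomized, and multiple imputation covers what is still missing.

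Two steps follow. The plan will first "evaluate missingness assumptions (by comparing available data for participants with complete vs. missing T2"). Then, if MAR is not appropriate, "the imputations will be performed using the methods specifically developed for data" missing not at random. The second step changes the imputations themselves, so it replaces the primary analysis; it does not add one beside it. The only other missing-data analysis named is a complete-case analysis, as a secondary analysis.

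The expected amount of missing data is given in the same section: "With the proposed sample size of 35 subjects per arm and assuming up to 15% loss to follow-up", which leaves about 30 per arm.

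**The concern.** Three conditions need to be kept apart. Under MCAR, missingness is unrelated to any data. Under MAR, it may depend on observed data but, given those, not on the missing value. Under MNAR, it depends on the missing value even after the observed data are taken into account. Comparing the available data of people with and without T2 can show that MCAR is false. It cannot separate MAR from MNAR, because that distinction rests on T2 values nobody has seen.

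The only diagnostic named for the choice therefore answers a different question, and it can mislead in both directions. A baseline difference may be taken as evidence against MAR, although conditioning on that variable is exactly what MAR imputation does. Similar groups may be taken as support for MAR, although dropout could still depend on the activity change that was not observed.

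At stake is which model produces the primary estimate and p-value. Missingness related to activity is plausible here: the Introduction lists fatigue and poor motivation among the barriers to activity, and the Measures section lets a wear period with fewer than 4 full days be discarded if it is not repeated.

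**Working it through.** **1. The plan's own figure.** Inputs from Data analysis: 35 per arm, up to 15% loss, effect size 0.75, two-sided alpha 0.05. Allocation from Procedure: "participants are randomized 1:1 to IT or WL".

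- Evaluable per arm: 35 × 0.85 = 29.75, about 30.
- Noncentrality: d × √(n/2) = 0.75 × √15 = 2.90. The noncentral t distribution gives power of 81.5%.

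This reproduces the article's statement: "The sample size of 30 subjects per arm provides 81% power to detect the mean difference between changes". The sample size calculation is not at fault.

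**2. The logic of the rule.** This step needs no numbers.

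| Comparison shows | What it establishes | What the rule invites | What is justified |
|---|---|---|---|
| A difference in observed variables | MCAR is doubtful | Move the primary imputation to MNAR | Put those variables in the MAR imputation model |
| No difference | Nothing about the unseen T2 values | Stay on MAR, with no MNAR analysis stated | MAR as a working assumption, with MNAR sensitivity analysis |

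**3. How such a trigger could behave.** The article gives no test, so one was assumed: a t-test of a single baseline variable, completers against missing, at p<0.05. Other assumptions: 35 per arm, 15% missing overall, true difference 0.75 SD, logistic missingness with a slope of 1.5 per SD, correlation of baseline with change of 0 or −0.3, and about 4,000 runs per scenario. MAR imputation was approximated by within-arm regression of change on baseline.

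| True mechanism | Trigger fires (corr. 0 / −0.3) | MAR-imputed difference | Complete-case difference |
|---|---|---|---|
| MCAR | 5% / 5% | 0.74 / 0.74 | 0.74 / 0.74 |
| MAR, driven by baseline | 95% / 95% | 0.75 / 0.75 | 0.75 / 0.75 |
| MNAR, same in both arms | 5% / 18% | 0.75 / 0.76 | 0.75 / 0.76 |
| MNAR in IT only | 5% / 9% | 0.96 / 0.95 | 0.96 / 0.97 |

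Under these assumptions the trigger fires mostly when MAR is true and rarely when MNAR is true. Bias appears only when the mechanism differs by arm, and the complete-case analysis then shares it.

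The rate depends heavily on the rule assumed. If any one of 20 independent comparisons at 0.05 sufficed, the chance of firing under MCAR would be 1 − 0.95^20 = 64%; for 10 comparisons, 1 − 0.95^10 = 40%. A single test gives 5%.

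**4. What the choice of model could do.** As one example of an MNAR method, suppose the 15% missing in IT are imputed as if on the waitlist. The expected difference becomes 0.85 × 0.75 = 0.6375 SD. Power by the noncentral t is then:

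| Per arm | d = 0.75 | d = 0.6375 |
|---|---|---|
| 30 | 81.5% | 68.0% |
| 35 | 87.1% | 74.8% |

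Multiple imputation analyses all 35 per arm, so the second row is the closer one for the diluted effect, though simple dilution ignores imputation variance. A simulation with 5 of 35 missing per arm, waitlist-reference imputation and Rubin's rules (3,000 runs) gave about 71%, against 82% for complete cases.

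**The case against.** The strongest reply is that the article describes no mechanical switch. It names no variables, test or threshold, and a judgement that MAR is not appropriate could draw on other information, such as recorded reasons for dropout. A reader might infer that any single significant baseline difference moves the primary analysis to MNAR; the text does not say so. This part of the reply stands, and the 64% and 40% figures cannot be presented as properties of the plan. The central point remains: the comparison is the only means of evaluation the article names, and it cannot inform the choice it feeds.

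A reader might also infer that the trial will run no MNAR sensitivity analysis. That goes too far. The article is a condensed account, and a full protocol or SAP may list such analyses along with the imputation model and the MNAR method. All that can be said is that this article states none when the comparison shows no difference. An SAP that followed the stated rule would still inherit the fault.

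Finally, a fall in power from 81% to 68% should not be read as an expected consequence. It assumes a waitlist-reference method that the article does not name, and 30 per arm where imputation would use 35. Nor is a smaller estimate under a reference-based assumption evidence that the MAR estimate is wrong.

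The practical limits on harm are fair too: planned loss is capped, T2 is pursued in everyone, and both branches remain intention-to-treat analyses by multiple imputation.

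**Conclusion.** The concern holds as a fault in a stated rule. A comparison of participants with and without T2 data should not select the primary imputation model, because it speaks to MCAR and not to MAR against MNAR. This conclusion is a matter of logic and rests on no assumed figure. Nothing elsewhere in the article repairs it.

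Its size cannot be fixed from the document. The planned loss of up to 15%, about 5 per arm, bounds the effect. In the illustrative simulation the estimate stayed near 0.75 when the same MNAR mechanism acted in both arms, and rose to about 0.95 to 0.96 when it acted in IT alone under a steep assumed slope. The firing rates and power figures depend on assumptions that are not in the document: the number of variables compared, the test, a rule that any one difference suffices, the slope, and the MNAR method.

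This should be fixed before the data are analysed. It does not call the design or the sample size into question.

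**What to change.** Reword the missing-data text in section 2.6 in three parts.

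1. **Primary analysis.** Multiple imputation under MAR whatever the comparison shows, with T1 activity counts and the T1 variables related to dropout or outcome in the imputation model.
2. **Sensitivity analysis.** A prespecified MNAR analysis in every case, for example a delta-adjusted tipping point or reference-based imputation of missing IT values from WL. The details can sit in the SAP.
3. **Completer-versus-missing comparison.** Keep it as description and for choosing imputation covariates, and remove its role in selecting the primary model.

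The cost is a change of wording and a few extra runs. No new data are needed, and design and sample size are unaffected. The Procedure section expects recruitment to continue until December 2026, so the change can be made before the analysis.

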### Aims and hypotheses

1.7

The aim of this study is to examine the efficacy of the GetUp&Go intervention for increasing PA and enhancing associated functional outcomes in msTBI. We propose the following hypotheses:

1a. Participants who receive the GetUp&Go intervention directly after randomization will show significantly more increase in PA, as assessed by average accelerometer activity counts/ day, from pre-randomization baseline to post-treatment 10 weeks later, compared to those waitlisted for 10 weeks.

1b. Participants randomized to immediate treatment (IT) will also show significantly more improvement compared to waitlisted participants (WL) on secondary outcome measures including intensity of PA (derived from accelerometer readings), self-reported PA, emotional function, fatigue, sleep, pain, and health-related quality of life.

2a. Participants randomized to continued use of RehaBot for 10 weeks after treatment (RB) will demonstrate significantly less diminution in accelerometer-based activity counts from post-treatment to 10-week follow-up compared to those for whom RehaBot is withdrawn (No Tx), adjusted for the degree of change in the initial treatment phase.

2b. Participants randomized to RB in the follow-through phase will demonstrate significantly less diminution/ worsening in other outcome domains listed under Hypothesis 1b, compared to No Tx participants.

In addition to testing these hypotheses, we will explore the predictors of treatment response, using pooled data from all participants from pre- to post-treatment. We will analyze in exploratory fashion the predictive effects of demographic and injury characteristics; baseline cognitive, physical, social, emotional, and personality factors; objective and perceived neighborhood characteristics; intrapersonal variables such as motivation, self-efficacy, outcome expectancies, and identity/ values as related to PA; and process variables such as the amount of interaction with RehaBot during treatment.

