### Overview of design

2.1

This is a randomized waitlist-controlled trial, registered prior to participant recruitment at https://www.clinicaltrials.gov (NCT06028334). As shown in Figure 1, after a baseline assessment, participants are randomized 1:1 into IT (10 weeks of GetUp&Go intervention) or WL (10 weeks on waitlist), after which the primary outcome is measured. WL participants then receive 10 weeks of GetUp&Go. The 10-week treatment period (for all participants) is termed the Acquisition or A phase. Directly after the A phase, participants are re-randomized 1:1 into the Follow-Through (FT) phase: 10 additional weeks, of either RB or No Tx. A final outcome assessment and a debriefing interview are conducted at the end of the FT phase.

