When all post-treatment data are collected (at T2 for IT and T2b for WL), participants are re-randomized 1:1 to 10 weeks of RB or No Tx (see Figure 1). T3 data are collected after that interval and as a final step, the participant receives a 15-minute debriefing interview by phone. This interview includes the Patient Global Impression of Change scale (75), worded as follows: “Since your participation in this study, how would you describe the change (if any) in areas of your life that could be related to physical activity and fitness, such as physical and mental well-being, mood, and overall quality of life?” Responses are on a 7-point scale from “No change (or condition has gotten worse)” to “A great deal better and a considerable improvement that has made all the difference.” Other questions are concerned with features of the treatment and the RehaBot app that the participant particularly liked or disliked.

This trial uses masked outcome assessment, with special precautions taken to prevent inadvertent unmasking. These include making treatment information completely inaccessible to data collection staff, and using a “script” reminding participants not to discuss any of their experiences in the program when contacted by a data collector. Any instances of inadvertent unmasking are recorded for later analysis of their influence, and data collectors are asked to guess the participant's treatment allocation following each assessment.

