For *Hypothesis 2a*, the primary endpoint is the change in average accelerometer activity counts/ day from post-intervention timepoint (T2 for IT participants, T2b for WL) to the follow-up endpoint, T3, 10 weeks later. The subject-specific T2/T2b-T3 changes will be modeled in an ANCOVA model as dependent on group (RB vs. No Tx) and the average accelerometer activity counts/day during the A phase (from timepoint T1 to post-intervention timepoint T2/T2b). The interaction between group and T1-T2(b) changes will be considered and retained in the model, if significant. If the interaction is not significant, Hypothesis 2a will be tested by comparing the mean change in RB vs. No Tx group using the model-based two-sided two-sample t-test with alpha 0.05. In the case of the main effects model (no significant interaction), this is equivalent to testing the main effect of RB (vs. No Tx) as the difference between intercepts of the regression lines with T1-T2(b) change as a predictor. A significant interaction would imply that the effect of RB (vs. No Tx) depends on the amount of change achieved during the A phase, and the test of interaction corresponds to comparing the slopes of the T1-T2(b) change regression lines between RB and No Tx groups. In the case of a significant interaction, the difference between RB and No Tx groups will be quantified in terms of the difference between the T1-T2(b) change regression slopes, and the significance (*p*-value) for that difference is the same as the significance (*p*-value) of the interaction. It is not expected that this interaction is important, and the study is not powered to detect such interaction. The secondary outcome measures (*Hypothesis 2b)* will be analyzed using the same approach.

We will report AEs and SAEs descriptively by treatment arm, including the number and percentage of participants experiencing at least one AE/SAE, as well as the total number of events by category. All AEs will be categorized by severity, relatedness to the intervention, and resolution status.

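### The Hypothesis 2a/2b covariate starts at T1 in both arms, so for waitlist participants it is not the treatment-phase change that the hypothesis names

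*Protocol article*

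**What the plan says.** Section 2.1 (Overview of design) allocates as follows: "participants are randomized 1:1 into IT (10 weeks of GetUp&Go intervention) or WL (10 weeks on waitlist"). It then says that "WL participants then receive 10 weeks of GetUp&Go". It names the treated interval: "The 10-week treatment period (for all participants) is termed the Acquisition or A phase".

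Section 2.4 (Procedure) places an accelerometer measurement at the end of the waiting period: "After this initial 10-week period, the primary outcome is measured with another 7-day Actigraph wear period". It puts the second randomisation later: "When all post-treatment data are collected (at T2 for IT and T2b for WL").

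Hypothesis 2a in section 1.7 specifies a comparison "adjusted for the degree of change in the initial treatment phase".

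Section 2.6 (Data analysis) models the change from T2/T2b to T3 on group and on activity "during the A phase (from timepoint T1 to post-intervention timepoint T2/T2b"). The first mention there describes an average level. The rest of the paragraph treats the covariate as the T1-T2(b) change, for the main-effects model, the interaction and the slope comparison, and it is read as a change here. Hypothesis 2b uses the same approach. A significant interaction is said to mean that the RB effect "depends on the amount of change achieved during the A phase", and in that case the slope difference and its p-value become the reported group comparison.

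**The concern.** By the article's own definition, the A phase of an immediate-treatment (IT) participant runs from T1 to T2, and that of a WL participant from T2 to T2b. Section 2.6 starts both at T1. For WL the covariate is then the sum of what happened while waiting and what happened on treatment. As an illustration, someone who falls by 1 SD on the waitlist and gains 1 SD on treatment would enter the model with an A-phase change of zero.

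Two things are at stake. First, the adjustment promised in Hypothesis 2a is not the one fitted for about half of those randomised, and one slope is estimated for a variable that means different things in the two arms. Second, the interaction cannot carry the interpretation that section 2.6 gives it. This matters more, because a significant interaction replaces the main effect as the reported RB versus No Tx result.

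**Working it through.** **1. The plan's own figure.** Section 2.6 states 80% power for N = 46 at an effect size of 0.85, with a two-sided two-sample t-test and alpha 0.05. With 23 per group, the noncentral t gives 80.5%, so the figure is reproduced. No covariate enters this calculation, so the choice of anchor cannot change it.

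**2. The timeline** (sections 2.1, 2.4 and 2.6).

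| Arm | T1 to T2 | T2 to T2b | A phase by 2.1 | Covariate window by 2.6 |
|---|---|---|---|---|
| IT | 10 treated weeks | none | T1 to T2 | T1 to T2: 10 treated weeks |
| WL | 10 waitlist weeks | 10 treated weeks | T2 to T2b | T1 to T2b: 10 + 10 = 20 weeks |

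For WL, (T2b − T1) = (T2 − T1) + (T2b − T2), that is, waitlist change plus treatment change. With 1:1 allocation of 70, this affects about 35 participants as randomised. Their share of the 46 analysed is not stated.

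**3. Bias.** T1, T2 and T2b are all measured before the second randomisation. Either version of the covariate is therefore independent of RB versus No Tx by design. In a simulation with no RB effect (N = 46, half WL; test-retest reliability 0.6 or 0.8; gain with mean 0.75 and SD 0.5; waitlist drift with mean 0 to 0.3 and SD 0 to 0.5; all assumed), the mean estimate was within 0.01 of zero and type I error was 4.6% to 5.5% under either anchor.

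**4. Precision when there is only noise.** Take unit variance at each time point and outcome Y = T3 − T2b.

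- Compound symmetry, correlation ρ: for either anchor the covariance with Y is −(1 − ρ) and the covariate variance is 2(1 − ρ). Slope and correlation are both −0.5, whichever anchor is used.
- AR(1), correlation ρ per 10 weeks: the slope is −(1 − ρ)/2 for either anchor. The correlation with Y is −(1 − ρ)/2 for the T2 anchor and −(1 − ρ)√(1 + ρ)/2 for the T1 anchor. At ρ = 0.6 these are −0.200 and −0.253; at ρ = 0.9 they are −0.050 and −0.069.

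In neither model does the T1 anchor predict Y less well, so no precision is lost.

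**5. Precision when people drift differently while waiting.** The document gives no drift figure, so a range is assumed. The settings are N = 46, half WL, error SD 0.45, and gain with mean 0.75 and SD 0.6, with 4,000 replicates per row.

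| Drift SD | SE of RB effect, T1 anchor | SE, pre-treatment anchor | Increase |
|---|---|---|---|
| 0 | 0.1663 | 0.1663 | 0% |
| 0.3 | 0.1711 | 0.1672 | 2% |
| 0.5 | 0.1737 | 0.1662 | 5% |
| 0.7 | 0.1794 | 0.1666 | 8% |

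At drift SD 0.7 the covariate slope shrank from −0.48 to −0.34, which is (0.48 − 0.34)/0.48 = 29%. The simulation in step 3, where drift SD was 0 to 0.5, gave increases of about 0 to 4%.

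**The case against.** The case for leaving this alone is that it concerns the covariate of a hypothesis that is not the trial's primary one. The RB comparison is randomised afresh, and Hypothesis 1a is untouched. Section 2.6 itself says that the interaction is not expected to matter and that the trial is not powered for it. All of this stands, and it limits the harm. It does not remove the contradiction between sections 1.7, 2.1 and 2.6, and a significant interaction would still change what is reported. The timeline figure is not in the text at hand, but the written definitions are clear without it.

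A reader might infer more than the document supports, in two ways.

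- *Weak correlation between the two anchors.* With no variation in gain, the WL change from T1 correlates with the change from T2 at 0.50 under compound symmetry, and at √(1 + ρ)/2 = 0.63 to 0.69 under AR(1) with ρ from 0.6 to 0.9. That looks like a poor covariate. But precision depends on how well each anchor predicts the T2b to T3 change, and in those same two models the T1 anchor predicts it as well or slightly better (step 4).
- *Lost sample size.* An 8% larger standard error suggests an effective N of 46/1.0768² ≈ 40. That is the worst corner of an assumed grid, measured against the better covariate and not against the plan. The planned power uses no covariate. In a further simulation with the step 5 inputs, assuming 30% or 50% of the gain is lost in follow-up, the T1-anchored model's standard error at drift SD 0.7 was still 9 to 15% below the unadjusted one.

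**Conclusion.** The covariate window in section 2.6 is wrong as written for WL participants. It contradicts the definition in section 2.1 and the adjustment named in Hypothesis 2a, and nothing in the document moves the WL start to T2. The main consequence is for interpretation: the fitted adjustment is not the hypothesised one for about half of those randomised, and the interaction would be misread if it were significant.

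The main-effect RB versus No Tx estimate is unbiased and the stated 80% power is unaffected. The precision cost is small and uncertain, from none up to about 8% in standard error, and that range rests entirely on assumed person-to-person drift during the wait. The point merits correction before analysis, but it does not threaten the trial's primary result.

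**What to change.** In section 2.6, define A-phase change as pre-treatment to post-treatment change: T1 to T2 for IT and T2 to T2b for WL. Use that definition in place of T1-T2(b) change for Hypothesis 2a, Hypothesis 2b and the interaction term. If the T1 anchor was intended, sections 1.7, 2.1 and 2.6 still need reconciling, because T1 to T2b is not the A phase as defined.

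The cost is a change of wording. WL accelerometry and outcome measures are already collected at T2, so no visits, data or participants are added. There is one small downside. Section 2.3 allows a wear period with fewer than 4 full days to be discarded, so a WL participant may have T2b but no valid T2 and would need the pre-treatment value imputed. The multiple imputation in section 2.6 is described for the Hypothesis 1 comparison and should be extended explicitly to this covariate.

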With regard to power, in the study of Clanchy et al. (24), participants in the active intervention group lost a mean of 1.7 standard deviations in average activity counts per day between their post-treatment and follow-up assessments, without any treatment during this time (comparable to our No Tx condition). We hypothesize that the loss in activity in the RB (treated) group in our study will be reduced by at least 50% of this value, an expected difference in effect size between RB and No Tx groups of 0.85. We make the conservative assumption of up to 15% additional attrition during the FT phase, leaving *N* = 46. With this sample size we will have 80% power to detect a difference in effect size of at least.85 between groups, using the two-sided two-sample t-test with alpha 0.05.

The analyses of predictors of treatment response will be exploratory, as the large number of predictors of possible interest will preclude hypothesis-driven methods. We will consider the use of analysis techniques such as model averaging (86, 87)*,* a method that allows for more robust conclusions about important candidate predictors when the possible predictors are numerous and the sample is relatively small, and when different variable selection methods may result in different and possibly suboptimal models.

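### Hypothesis 2a can reach significance by either of two tests at full alpha, which nearly doubles its type I error, and one of them replaces the RehaBot effect with a slope difference

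*Protocol article*

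**What the plan says.** Section 1.7 (Aims and hypotheses) states Hypothesis 2a as a directional claim about loss of activity: participants kept on RehaBot "will demonstrate significantly less diminution in accelerometer-based activity counts from post-treatment to 10-week follow-up" than those from whom it is withdrawn.

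Section 2.6 (Data analysis) models the change from T2/T2b to T3 by ANCOVA, with group and the change over the acquisition phase as predictors. It then sets a two-stage rule:

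- **Pre-test:** "The interaction between group and T1-T2(b) changes will be considered and retained in the model, if significant". No level is given for this test.
- **Interaction not significant:** the group means are compared "using the model-based two-sided two-sample t-test with alpha 0.05".
- **Interaction significant:** "the difference between RB and No Tx groups will be quantified in terms of the difference between the T1-T2(b) change regression slopes", and the p-value "for that difference is the same as the significance" of the interaction.

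The same paragraph says the interaction is not thought likely to matter and that "the study is not powered to detect such interaction". Hypothesis 2b outcomes follow the same procedure. The sample-size paragraph is built on a difference in means: "an expected difference in effect size between RB and No Tx groups of 0.85", with "up to 15% additional attrition during the FT phase, leaving *N* = 46".

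**The concern.** There are two problems.

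1. **Error rate.** The comparison of RB with No Tx can be called significant through the interaction or, failing that, through the main effect. Each test has its own full alpha, so the stated 0.05 is not the error rate of the procedure.
2. **Question answered.** A slope difference says that the RB effect varies with how much a participant gained during treatment. It does not say which group lost more activity. RB could lose as much as No Tx on average, or more, and still give a significant slope difference.

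The second randomization exists to show whether continued RehaBot support preserves gains. In the significant-interaction branch the plan names no average RB effect, and no RB effect at any stated level of earlier change. An interaction that the plan neither expects nor powers therefore decides whether the one powered comparison is used.

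**Working it through.** **Inputs from section 2.6:** N = 46, taken as 23 per group (re-randomization is 1:1); effect size 0.85; two-sided alpha 0.05; stated power 80%.

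**Assumptions:** the interaction is tested at 0.05, the only alpha named in section 2.6, with 0.10 shown as a range. The covariate is the change from T1 to T2/T2b.

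**Step 1: the plan's own power figure.** For a two-sample t-test the noncentrality is 0.85 × √(23 × 23 / 46) = 0.85 × 3.391 = 2.88 on 44 degrees of freedom. Power is 80.5%, so the stated 80% is reproduced. It applies to the mean difference only.

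**Step 2: type I error by formula.** Under the null the interaction and main-effect tests are close to independent:

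1 − (1 − 0.05)(1 − 0.05) = 1 − 0.9025 = 9.75%, which is 1.95 times 5%.

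With the interaction tested at 0.10: 1 − 0.90 × 0.95 = 14.5%.

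**Step 3: type I error by simulation** (200,000 trials per row, no RB effect at any level of earlier change):

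| Setting | Significant by either route |
|---|---|
| N = 46, normal errors | 9.7% (5.0% interaction + 4.7% main effect) |
| Outcome correlated with covariate | 9.7% |
| Heavy-tailed errors | 9.6% |
| N = 50 | 9.9% |
| Interaction tested at 0.10 | 14.5% |
| Main effect only, no pre-test (N = 46, normal errors) | 5.0% |

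A second simulation generated T1, T2 and T3 as multivariate normal with equal correlations (20,000 trials per setting, N = 46). The rule rejected in 10.0% of trials at correlation 0.5 and 9.8% at 0.7. The plain ANCOVA rejected in 4.9% to 5.2%.

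**Step 4: what the interaction route shows.**

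- Under the null, 5.01% of trials have a significant interaction, and in 2.49% the slope difference is negative. The direction is split about evenly.
- With a zero average RB effect but a true slope difference of 0.5 SD per SD of earlier change, the rule gives a significant RB versus No Tx result in 39% of trials.
- With a true constant effect of 0.85 SD, 5.0% of trials switch to the slope measure by chance. The chance that a significant main effect is the reported test falls from 79.5% to 75.6%.

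**Step 5: Hypothesis 2b.** Table 1 lists nine outcome measures besides the primary. If they were independent, the chance of at least one false positive rises from 1 − 0.95⁹ = 37% to 1 − 0.9025⁹ = 60%. Counting the seven domains of Hypothesis 1b instead, it rises from 1 − 0.95⁷ = 30% to 1 − 0.9025⁷ = 51%.

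**The case against.** The strongest reply is that the plan never says a significant interaction confirms Hypothesis 2a. Testing of that hypothesis is mentioned only in the non-significant branch. The other sentence could mean no more than that the p-value of a slope difference is the interaction p-value. On that reading Hypothesis 2a can be rejected only through the main effect, in 4.7% of null trials. The text is open to this reading, but the plan is not rescued by it. The sentence is about the difference between RB and No Tx, and if it is not the test, Hypothesis 2a has no test at all when the interaction is significant.

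Other points stand as limits on size:

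- The level of the interaction test is unwritten, so the inflation depends on an assumed 0.05.
- The article does not say that group means would be withheld when the interaction is kept, and a fuller analysis plan could add conditional effects. The article does, however, fix how the group difference is expressed in that branch.
- The Hypothesis 2b figures assume independence, which is implausible when several outcomes come from the same accelerometer. The 37% or 30% starting value is ordinary multiplicity and does not come from this rule.
- If there is truly no interaction, the switch happens in only about 5% of trials, and the loss of power for the reported main effect is modest.
- Checking for equal slopes is familiar practice in ANCOVA, and the rule is prespecified. Prespecifying it does not control its error rate.

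**Conclusion.** The concern holds. As written, the rule gives a significant RB versus No Tx result in about 9.7% of trials when there is no RB effect, against the stated 5%, assuming the interaction is tested at 0.05. The figure barely moves with sample size, error distribution or correlation between visits, and it is larger if the interaction level is looser. Separately, and whatever level is used, the significant-interaction branch replaces the powered mean difference with a quantity that does not answer Hypothesis 2a.

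The defect is confined to Hypotheses 2a and 2b. Hypothesis 1a, the trial's primary hypothesis, is tested separately and is not touched.

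**What to change.** In section 2.6:

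- Test Hypothesis 2a, and each Hypothesis 2b outcome, by the RB versus No Tx main effect in the ANCOVA without interaction, at two-sided 0.05, whatever the interaction shows. Report the adjusted mean difference with its 95% CI.
- Move the interaction to an analysis labelled exploratory, with the acquisition-phase change mean-centred and the RB effect shown at low, mean and high values of that change.
- Delete the sentences that let the slope difference and its p-value stand for the group comparison.

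With this change type I error is 5.0%, and simulated ANCOVA power at 0.85 SD is 79.5%. Keeping both routes at 0.025 each would also hold the overall error (4.9%), but a slope difference would still stand in for the RB effect, so it is the weaker remedy.

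The cost is analysis-plan wording only. Section 2.4 (Procedure) expects recruitment to run to December 2026, so the change can be made before the data are analysed.
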